## Interventions

Stage 1: Examination. In no specified order participants will be examined separately once by the physiotherapist and once by the orthopaedic surgeon. Participants will be blind to the profession of their examiner and will be asked to not discuss their first assessment with the second clinician.

Stage 2: Subacromial corticosteroid and local anaesthetic injection by either the physiotherapist or the surgeon. Following randomisation, participants will see either the physiotherapist or the surgeon for their injection consultation, which will include gaining consent for the procedure according to usual hospital protocols. Participants will be blind to the profession of the clinician who provides the injection. Participants will receive usual post injection care.

Both groups will receive the following standard post injection advice for the week following injection (Crawshaw 2010):

- avoid activities that provoke pain
- avoid repetitive overhead activities
- stop sporting activities involving the arm

In keeping with standard practice, both groups will be offered physiotherapy, beginning one week post injection. The treating physiotherapist will provide care at their discretion from a selection of common treatments including advice, exercise and manual therapy techniques. The number of treatment sessions is at the discretion of the physiotherapist.

**Clinical Procedures**

The Physiotherapist and the Orthopaedic surgeon providing injections will

- - Prescribe and deliver the injection using aseptic technique. The injection procedure involves preparing and administering the following drug and dose schedule for an average sized adult. Technique includes a small aspiration (draw back of the syringe), to check that any fluid does not appear suspect (purulent) and that the needle is not in a blood vessel. If found, suspect fluid will be aspirated and sent for microscopy, culture and analysis, and the injection will not be given.
  - Decide and implement ongoing management

**Injection Procedure**

PATIENT SELECTION

- thorough clinical assessment, including seeking and incorporating the necessary information from referrals, previous reports, other professionals, imaging, pathology and the patient.
- establish whether there is clinical indication for subacromial injection.
- establish whether it is safe to offer subacromial injection, incorporating standard precautions, and considering any contraindications and clinical judgement.

PATIENT CONSENT

- explain the management options, including alternatives to injection
- discuss and answer questions in relation to risks and benefits of the injection, based on the information sheet already provided, and any other questions
- obtain and record verbal and written consent

PREPARATION FOR PROCEDURE

- position patient (sitting on couch or chair)
- ensure all equipment is available the room:

drugs, needles/syringes/wipes, sharps disposal, gloves etc

INJECTION TECHNIQUE

- wash hands before drawing up drugs
- mark needle insertion point on the skin with an aseptic needle sheath
- wash hands and apply non-sterile gloves
- clean skin with alcohol wipe and allow it to dry
- without contaminating the cleaned area, insert needle, draw back (aspiration check) as safety check and providing appropriate to proceed, administer the injection.
  - If safety aspiration reveals fresh blood, reposition needle and repeat process until needle is clear of vessel before injecting
  - If safety aspiration reveals suspect fluid, change syringe and aspirate fluid to be sent for microscopy/culture/sensitivity. Abandon injection.
- withdraw needle and apply pressure to site with cotton wool, when bleeding stops apply band aid, or alternative as clinically indicated
- dispose needles, syringes ampoules and vials in the sharps bin
- de-glove and wash hands

POST INJECTION

- remain mindful of any signs of adverse reaction
- re-test shoulder signs as clinically indicated
- provide advice upon post injection shoulder care and management
- explain (and highlight post injection information sheet) how to recognise adverse reactions and what to do if any arise.

**Medicines and dose schedule**

- - Betamethasone and lidoocaine will be drawn into the same syringe, prior to administration
  - Methylprednisolone will be used as an alternative corticosteroid if required, eg: betamethasone not available.

**Medicines and dose schedule**

| **Drug** | **Site** | **Dose** | **Volume** |
| --- | --- | --- | --- |
| Betamethasone (Celestone Chronodose)  Ampoule: 5.7mg/ml  AND  Lidocaine Hydrochloride 1% | Subacromial  Subacromial | 5.7mg  5ml | 6ml |
| **OR in the event that betamethasone is not available** | | | |
| Methylprednisolone Acetate (Depo-medrol)  Vial: 40mg/ml  AND  Lidocaine Hydrochloride 1% | Subacromial    Subacromial | 40mg  5ml | 6ml |

***Recruitment and screening***

The Research Assistant will identify appropriate referrals from orthopaedics, phone potential participants and administer appointment bookings in communication with orthopaedics. Upon arrival the Research Assistant will complete stage 1 consent form and baseline data forms with participants. Following stage 1, the research assistant will analyse clinician’s response (yes/no) to the primary stage 1 outcome measure “would you offer subacromial injection today? ”, to determine whether:

1. Both clinicians would offer injection, in which case the Research Assistant consents the participant for stage 2.

2. Neither clinician would offer injection, in which case, the participant sees surgeon for ongoing care and is not invited to participate in stage 2.

3. Only one clinician would offer injection, in which case the participant sees the surgeon for ongoing care and is not invited to participate in stage 2.

After consenting for stage 2, the research assistant will take pre-injection measures of the exploratory outcome measure. The participant will then take the top envelope from the randomised pile and go to the appropriately numbered room. The clinician will check that the participant has come to the room indicated on their randomisation card, gain written consent for the procedure, deliver the injection and record on the Treatment Form. The research assistant will then take post-injection exploratory outcome measures.

The surgeons assessment form and the treatment form will be scanned into EMR and form the clinical notes for the consultation.

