*** primary outcome measure stage 1**

**^ primary outcome measure stage 2**

| **Category** | **Measure** | **From** | **Timing** |
| --- | --- | --- | --- |
| **Clinical and Demographic Characteristics** | Age, sex, employment status, hand dominance, uni or bilateral | Participant | Baseline |
| Imaging to date and key findings | Referral | Baseline |
| Duration of symptoms | Participant | Baseline |
| Past treatments and costs – physiotherapy, injection, surgery, other | Participant | Baseline |
| Medications | Participant | Baseline |
| **Baseline outcome measures** | Impact and costs questionnaire | Participant | Baseline |
| Work Productivity and Activity Impairment Questionnaire (WPAI) | Participant | Baseline |
| Work Limitations Questionnaire (WLQ) | Participant | Baseline |
| Shoulder Pain and Disability Index (SPADI) | Participant | Baseline |
| 10 cm VAS patient perception of pain over the past 3 days | Participant | Baseline |
| EuroQual-5D-5L | Participant | Baseline |
| **Stage 1** | | | |
| **Clinical agreement** | Are there any safety contraindications to injection? | Clinicians | At time of assessment |
| Are there any safety precautions regarding injection? | Clinicians | At time of assessment |
| *** Would you provide subacromial injection today?** | Clinicians | At time of assessment |
| Are there any other reasons to exclude this participant from stage 2 | Clinicians | At time of assessment |
| **Stage 2** | | | |
| **Safety** | Incidence of adverse events | Adverse event reporting mechanism | Collated throughout |
| **Access** | Current new appointment booking dates with Orthopaedics and OPSC | Research Assistant | At time of intervention |
| **Effectiveness** | **^Shoulder Pain and Disability Index (SPADI)** | Participant | 6 weeks  12 weeks |
| 10 cm VAS patient perception of pain over past 3 days | Participant | 6 weeks  12 weeks |
| Global Rating of Change Scale | Participant | 6 weeks  12 weeks |
| EuroQual-5D-5L | Participant | 6 weeks  12 weeks |
| Physiotherapy attendances post injection | eMR / Groupwise | 6 weeks  12 weeks |
| 10 cm VAS patient satisfaction with care | Participant | 12 weeks |
| **Economic** | Staff costs for each clinician | Standard pay scales | 6 weeks  12 weeks |
| Impact and costs questionnaire | Participant | Baseline |
| Work Productivity and Activity Impairment Questionnaire (WPAI) | Participant | Baseline |
| Work Limitations Questionnaire (WLQ) | Participant | Baseline |

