***Blinding***

Clinicians:

Surgeon and Physiotherapist:

Clinicians will be blind to the assessment findings of the other clinician.

Treating Physiotherapist (post injection):

The treating physiotherapist will not be advised who delivered the injection and will be asked to not retrieve this information from patient records.

Participants:

The profession of the clinicians will not be disclosed to participants.

For stage 2 participants, this blinding will be assessed post injection when participants will be asked to tick whether they think they saw the physiotherapist or the surgeon.

Research Assistant:

The research assistant will not know which clinician is in each room and will therefore be a blind assessor of these post injection exploratory outcomes of range of motion and pain.

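### The treating physiotherapist's blind rests on a request not to look up the injector in notes that probably show it, and nothing checks whether it held: a cheap improvement

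*Protocol*

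**What the plan says.** Under Recruitment and screening, the clinician who gives the Stage 2 injection will "deliver the injection and record on the Treatment Form". The same section then states: "The surgeons assessment form and the treatment form will be scanned into EMR and form the clinical notes for the consultation".

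Under Blinding, the safeguard for the post-injection physiotherapist is: "The treating physiotherapist will not be advised who delivered the injection and will be asked to not retrieve this information from patient records". A check on blinding is given in the participants' paragraph only: "this blinding will be assessed post injection when participants will be asked to tick whether they think they saw the physiotherapist or the surgeon".

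Under Interventions, "both groups will be offered physiotherapy, beginning one week post injection". On content: "The treating physiotherapist will provide care at their discretion from a selection of common treatments including advice, exercise and manual therapy techniques". On amount: "The number of treatment sessions is at the discretion of the physiotherapist".

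The outcome table lists SPADI at 6 and 12 weeks as the Stage 2 primary measure. Under Effectiveness it also lists "Physiotherapy attendances post injection", at the same two times, taken from eMR / Groupwise.

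**The concern.** The person whose blind is least protected also decides how much co-treatment each participant receives, and of what kind. The injection record is filed as the note of the visit, so a colleague who opens it for an ordinary clinical reason could learn the arm without meaning to. If that knowledge changed the amount or kind of physiotherapy, the SPADI comparison would mix the effect of who injected with the effect of unequal aftercare. The attendance measure would be affected directly. The question matters more than usual here because the trial asks whether a physiotherapist is no worse than a surgeon, and the treating clinician belongs to one of those two professions.

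**Working it through.** The point is settled mainly by reading the sections together.

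1. **Who writes the record.** The injecting clinician completes the Treatment Form (Recruitment and screening).
2. **Where it goes.** It is scanned into the EMR and, with the surgeon's assessment form, becomes the consultation note (same section). The surgeon's assessment form is completed for everyone at Stage 1 and does not reveal the arm. Only the Treatment Form could.
3. **Whether it shows the injector.** The form is listed but not reproduced, so this is an inference. The Blinding section supports it, since it asks the physiotherapist not to retrieve that information from the records.
4. **What stands in the way.** Non-disclosure and a request. No masked summary, restricted access or delayed scanning is stated.
5. **What the physiotherapist controls.** Choice of treatments and number of sessions (Interventions).
6. **When.** From week 1, so up to 6 − 1 = 5 weeks of sessions come before the first SPADI follow-up and up to 12 − 1 = 11 weeks before the second.
7. **Whether failure would be seen.** Attendance counts could show an imbalance in sessions but not its cause, and they say nothing about content. The blinding check covers participants only.

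**Scale.** The documents give no figure for a co-treatment bias, so what follows is a sensitivity range on assumed values. Inputs from the Sample size paragraph: SD 21.7, margin 15 points, α = 0.05, β = 0.2, 27 per group, 15% drop-out. Sidedness is not stated.

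Reproducing the plan's figure at one-sided 0.05 and a true difference of zero:
- The normal approximation gives 26 per group (52 in total).
- The noncentral t gives power 0.792 at 26 and 0.806 at 27 per group, hence 27 and 54 in total.
- 54 / 0.85 = 63.5, rounded up to the stated 64.
- One-sided 0.025 would need 33 per group (66 in total), which does not match. One-sided 0.05 is therefore used below.

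Standard error of the difference: 21.7 × √(2/27) = 5.91 points.

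For an assumed bias of b SPADI points:
- In favour of the physiotherapist arm, with the true difference at the margin, the false no-worse rate is Φ(−1.645 + b/5.91).
- Against that arm, with no true difference, power is Φ((15 − b)/5.91 − 1.645).

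| b (assumed) | False no-worse rate, bias in favour | Power, bias against |
| --- | --- | --- |
| 0 | 5.0% | 81% |
| 1 | 7.0% | 77% |
| 2 | 9.6% | 71% |
| 3 | 12.8% | 65% |
| 5 | 21.2% | 52% |

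These formulas hold for a bias of any origin. They show how sensitive the comparison is, not that such a bias will occur.

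**The case against.** The strongest reply is that the protocol saw this exposure and dealt with it. The physiotherapist is not told and is asked not to look, and what must not be retrieved is the injector's identity, not the whole note. That stands. A reader might infer that the filing rule and the blinding rule contradict each other. They do not: the second anticipates the first and is merely weak.

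A reader might also infer that the physiotherapist has to open the note in order to treat. No section says so, and much of what a hand-over would carry is already fixed: the subacromial site, the doses and volume, the standard advice and the start at one week. The choice between the main and the alternative corticosteroid does vary. So the documents support that the physiotherapist could learn the arm, not that they will. Nor do they say that the treating and injecting physiotherapists share a department.

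A third tempting reading is that extra care for a lagging arm would push the result towards no worse. A fully blinded clinician with discretion over sessions may also give more to patients who are doing poorly. That route does not depend on knowing the injector, and masking would not remove it. Only care that differs because the injector is known counts here, and its direction is open.

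Existing protections also count. SPADI is completed by participants, who are blinded and checked, and the treating physiotherapist does not score it. Attendances are collected, so unequal session numbers would be visible. These limit the harm. They do not show whether the treating physiotherapist's blind held.

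**Conclusion.** The point holds as a cheap improvement. The treating physiotherapist's blind depends on an instruction alone, that clinician controls co-treatment ahead of both SPADI time points, and a failure would leave no trace. Any resulting bias could run either way, and the documents do not allow it to be sized. The table above rests on assumed bias values, a one-sided 0.05 test and 27 analysed per group. The conclusion also rests on the inference that the Treatment Form, or the note built from it, identifies the injector. If it does not, the exposure largely disappears, although a check of this blind would still be worth one question. Nothing here shows that the blind will fail or that the trial's conclusion is unsafe.

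**What to change.** Amend Recruitment and screening and the treating-physiotherapist paragraph of Blinding in two ways.

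- **Masked hand-over.** Give the treating physiotherapist a short sheet with product, site, side, date, standard advice and precautions, and no injector identity, so that routine care does not require opening the consultation note.
- **One check.** At the last session, have the treating physiotherapist record whether they knew who gave the injection or, if not, which clinician they believe it was. Report the answers descriptively by arm, next to attendances.

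Do not analyse SPADI by blinding status. That status arises after randomisation, and splitting about 54 participants on it would give small groups that cannot be compared fairly. Leave the injector's identity in the legal record: the physiotherapist prescribes under a specific approval and credentialing, and coding the identity there would raise record-keeping questions the protocol does not address.

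The cost is one short form and one question, plus a stated route to the full note when an adverse event requires it. Sample size, treatment and the main analysis do not change.

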***Blinding***

Clinicians:

Surgeon and Physiotherapist:

Clinicians will be blind to the assessment findings of the other clinician.

Treating Physiotherapist (post injection):

The treating physiotherapist will not be advised who delivered the injection and will be asked to not retrieve this information from patient records.

Participants:

The profession of the clinicians will not be disclosed to participants.

For stage 2 participants, this blinding will be assessed post injection when participants will be asked to tick whether they think they saw the physiotherapist or the surgeon.

Research Assistant:

The research assistant will not know which clinician is in each room and will therefore be a blind assessor of these post injection exploratory outcomes of range of motion and pain.

***Randomization***

In Stage 2, a computer generated (excel software) random number sequence will be used to randomise the order of treating clinicians. The sequence will be stratified by source of the patients (i.e. OPSC waiting list versus general orthopaedic waiting list). The randomisation sequence will be concealed in sealed opaque envelopes and administered by the Research Assistant.

## Statistical Analysis

All statistical analyses will be performed on an intention to treat basis using the statistical package SPSS (V19.0, IBM, New York, USA), with alpha level set at 0.05.

The analysis of the GEE will be conducted using SAS Statistical Software version 9.2.

**Stage 1:**  Agreements between the decisions from the two clinician assessors will be investigated using the proportion of observed agreement, the probability of chance agreement, and the kappa statistics with the 95% confidence intervals.

**Stage 2:** For continuous outcomes, normality of data will be assessed and parametric tests applied if normality is upheld. Treatments from the two clinicians will be compared over time (pre- to post-intervention) on an intention-to-treat basis using the generalised estimating equation (GEE) approach (Liang and Zeger1986) with an exchangeable working correlation structure to account for within-subject correlation for repeated measurements. With the GEE, a normal distribution with an identity link will be used for continuous outcome measures. The respective pre-condition baseline scores will be included as a covariate. The effects of time (within-group differences), practitioner (between-group differences), and practitioner by time interaction (between-group differences over time) will be included in all models and assessed using the Wald χ2 test. Model fit and assumptions will be checked were appropriate within the GEE framework. The GEE approach works well with missing observations on outcome measures, assuming that they are missing completely at random (MCAR). The validity of this assumption will be examined. If the MCAR assumption was violated, adjustment using weighted GEE (Hogan et al., 2004) will be performed. Appropriate post hoc tests will be conducted if significant main or interaction effects are identified from the omnibus analyses.

**Sample size:** Assuming α = 0.05, β = 0.2, and a standard deviation of 21.7 points of the change in scores from baseline, we estimate that 54 participants (27 per group) will be required to test for a comparative efficacy between the two treatments with a noninferiority margin of 15 points in the SPADI scores. The above parameter values for the power calculation are based on previous study on comparing the responsiveness for SPADI and several indices in patients receiving corticosteroid injection therapy (Ekeberg et al., 2010), where the minimum clinically important difference (MCID) for the SPADI is 23.1 points at 6 weeks. The calculation is conservative in the sense that it ignores the added power inherent in the repeated measures design. However, it is appropriate when treatment comparisons at the two individual time points (6 weeks and 12 weeks) are performed to assess the interaction treatment effect at different time after the injection. Allowing for a conservative drop-out rate of 15%, we will recruit a total of 64 participants (32 per group) for stage 2. In order to obtain this number, we anticipate needing 128 recruits into stage 1 because we estimate that 50% of stage 1 participants will be eligible to enter stage 2.

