**Primary objectives**

To discover whether:

1. there is agreement between the physiotherapist and the surgeon regarding selection of shoulder patients appropriate for subacromial injection.
2. care (subacromial corticosteroid and local anaesthetic injection) delivered by the physiotherapist is no worse than the same type of care delivered by the orthoapaedic surgeon, with respect to safety, access, effectiveness and efficiency.

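### The noninferiority comparison of SPADI is planned on an intention-to-treat basis only, with no per-protocol analysis to show whether non-received injections have diluted the difference

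*Protocol*

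**What the plan says.** The second primary objective (Protocol, Primary objectives) is to find out whether injection care "delivered by the physiotherapist is no worse than the same type of care delivered by the orthoapaedic surgeon". The sample size paragraph makes this a noninferiority question on SPADI, "with a noninferiority margin of 15 points in the SPADI scores".

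The analysis basis is fixed twice in the Statistical Analysis section. The general rule is "All statistical analyses will be performed on an intention to treat basis using the statistical package SPSS". The Stage 2 model is then described as comparing the clinicians "on an intention-to-treat basis using the generalised estimating equation (GEE) approach". No per-protocol or as-treated analysis is named anywhere in the Protocol, even as a sensitivity analysis.

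Two routes lead from randomisation to no injection:

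- **Declined.** Under Recruitment and screening, the participant draws an envelope and goes to a room, where the clinician is to "gain written consent for the procedure, deliver the injection and record on the Treatment Form". Consent to the procedure therefore follows allocation. Under Injection Procedure, the consent discussion covers alternatives to injection.
- **Abandoned.** Injection Procedure states: "If safety aspiration reveals suspect fluid, change syringe and aspirate fluid to be sent for microscopy/culture/sensitivity. Abandon injection". Clinical Procedures says the same in other words.

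**The concern.** In a superiority trial intention-to-treat is the cautious choice, because non-adherence makes the arms look alike and so works against the claim. In a noninferiority trial looking alike is the claim. Participants who receive no injection from either clinician cannot show a difference in how well the two clinicians inject. If they are spread evenly over the arms, each one moves the estimate towards zero and away from the 15-point limit.

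The Protocol does more than leave analysis sets to a later document. It assigns one basis to all analyses, so a per-protocol set added in a SAP would depart from it. At stake is whether a finding of no worse, which the Benefits section says is meant to inform policy makers and regulators, can be separated from a diluted difference.

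**Working it through.** **Inputs from the Protocol, Statistical Analysis.** "Assuming α = 0.05, β = 0.2, and a standard deviation of 21.7 points of the change in scores from baseline"; margin 15 SPADI points; 27 evaluable per group, raised to 32 per group for 15% drop-out. The analysis section repeats alpha, "with alpha level set at 0.05", and neither place gives the number of sides.

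**Input not in the Protocol.** The share of participants who do not receive the injection. I assume 5% and 10% of each arm.

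**Step 1: reproduce the stated sample size.** With a true difference of zero, n per group = 2 × (z₁₋α + z₀.₈₀)² × SD² / margin².

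- One-sided 0.05: 2 × (1.645 + 0.842)² × 21.7² / 15² = 25.9, so 26 per group. The noncentral t calculation gives 27 per group, with power 0.806.
- One-sided 0.025: 33 per group (normal) or 34 (t).

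The stated 27 is reproduced at one-sided 0.05 and not at 0.025. Dividing 54 by 0.85 gives 63.5, so 64, as stated. I use one-sided 0.05 below as the implied level.

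**Step 2: effect of equal non-receipt.** SE = 21.7 × √(2/27) = 5.906. Let the true difference among those injected equal the margin, and let a share f of each arm go without injection, with the same mean outcome in both arms. The intention-to-treat difference is then 15(1 − f), and the chance of wrongly passing is Φ(−1.645 + 15f / 5.906).

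| f in each arm | Difference seen | False-pass rate, one-sided 5% | Same, two-sided 95% interval |
| --- | --- | --- | --- |
| 0 | 15.00 | 5.0% | 2.5% |
| 5% | 14.25 | 6.5% | 3.3% |
| 10% | 13.50 | 8.2% | 4.4% |

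The last column replaces 1.645 by 1.960. One participant per arm of 27 is f = 3.7%: Φ(−1.645 + 0.556/5.906) = 6.0% at the one-sided 5% level.

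**Step 3: effect of unequal non-receipt.** Let participants without an injection do U points worse than those the surgeon injects, and let the shares be f_P (physiotherapist arm) and f_S (surgeon arm). The intention-to-treat difference becomes 15(1 − f_P) + U(f_P − f_S). With equal shares this is 15(1 − f), as in step 2. If only the physiotherapist arm is affected, it is 15 + f_P(U − 15), which exceeds the margin whenever U is above 15; intention-to-treat then counts against noninferiority. If only the surgeon arm is affected, it is 15 − U·f_S, which favours noninferiority whenever U is positive.

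**Step 4: precision of a per-protocol analysis.** Power at 27 per group (normal approximation, one-sided 0.05, true difference zero) is Φ(15/5.906 − 1.645) = 0.815. If a further 5%, 10% or 15% are excluded it is 0.797, 0.778 or 0.757. At 10% exclusion the interval is wider by a factor of 1/√0.9 = 1.05.

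**The case against.** The strongest reply is that the design leaves little room for non-receipt. The treatment is one injection, given at the visit of randomisation, after both clinicians have independently said they would inject that day and the participant has consented to Stage 2. There is no course of treatment to drop out of. This stands, and it is why the likely effect is small.

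A second reply is that intention-to-treat suits a service-delivery question. Each clinician takes consent, performs the aspiration check and decides whether to proceed, so declined or abandoned injections are partly results of that clinician's care. A per-protocol set conditions on these decisions and could hide inferiority if one clinician abandons more often. This also stands. It argues for keeping intention-to-treat as the main analysis and against letting the per-protocol result replace it.

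A third reply is that non-receipt could be counted from the Treatment Form. That shows how many were affected by arm, but not what they did to the comparison with the margin.

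Two stronger readings are tempting. A reader might infer from the room check that participants are expected to be injected by the wrong clinician, which would dilute the difference twice as fast. The text supports the opposite: the clinician checks the room against the randomisation card before consent and injection, as a safeguard, and no other route to cross-over is described. A reader might also infer that noninferiority should be claimed only if both analyses succeed. Nothing in the Protocol requires that, and it has a price: keeping 27 per-protocol participants per group after 15% drop-out needs 27/(0.85 × 0.95), 27/(0.85 × 0.90) or 27/(0.85 × 0.85), that is 34, 36 or 38 per group instead of 32, at 5%, 10% or 15% exclusion.

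**Conclusion.** The point holds in a limited form. The Protocol fixes intention-to-treat as the only basis for a noninferiority comparison and provides no analysis that would reveal dilution. With similar non-receipt in both arms, the false-pass rate rises from 5.0% to about 6.5% at 5% non-receipt and 8.2% at 10%.

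This rests on one-sided 5% (inferred from the sample size), 27 evaluable per arm, a true difference equal to the margin, and non-receipt rates that are assumed. It would be wrong to conclude that the trial will exceed a stated 5% error rate: the Protocol does not give the number of sides, and with a two-sided 95% interval the same rates give 3.3% and 4.4%. Nor is the direction certain, since unequal non-receipt can reverse it. Intention-to-treat itself is not the mistake; its exclusivity is.

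**What to change.** In the Statistical Analysis section, limit the sentence that puts all analyses on an intention-to-treat basis and add, for the Stage 2 SPADI comparison:

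- Intention-to-treat in all randomised participants remains the main analysis.
- The same model is also run in a per-protocol set: participants who received the allocated clinician's injection at the randomised visit. The set is identified from the Treatment Form and randomisation card and is defined before unblinding.
- The confidence limit from each analysis is compared with the 15-point margin, and both are reported.
- Non-receipt is reported by arm, separating declined from abandoned injections.
- If the two analyses disagree, a noninferiority claim is interpreted with caution.

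The cost is one more run of the same model, one flag per participant from records already made at the visit, and a slightly wider interval in the per-protocol set. The planned sample size does not change, because the per-protocol result is supportive and not a second condition for success.
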